## Abstract

**Background:**

MRSA is a significant contributor to prolonged hospital stay, poor clinical outcome and increased healthcare costs amongst surgical patients. A PCR test has been developed for rapid detection of MRSA in nasal swabs. The aims of this study are (1) to estimate the effectiveness of screening using this rapid PCR tests vs culture in reducing MRSA cross-infection rates; (2) to compare the cost of each testing strategy, including subsequent health care costs; and (3) to model different policies for the early identification and control of MRSA infection in surgical patients.

**Methods/Design:**

The study is a prospective two-period cross-over study set in 7 surgical wards covering different surgical specialities. A total of 10,000 patients > 18 years will be tested over 16 months. The only difference between the two study periods is the method used for the detection of MRSA in each ward (rapid v conventional culture), with all other infection control practices remaining consistent between the arms. The study has been designed to complement routine practice in the NHS. Outcomes are MRSA cross-infection rates (primary outcome) and need for antibiotic therapy and MRSA-related morbidity. Parallel economic and modelling studies are being conducted to aid in the interpretation of the results and to evaluate the cost-effectiveness of the rapid PCR screening strategy.

**Discussion:**

This paper highlights the design, methods and operational aspects of a study evaluating rapid MRSA screening in the surgical ward setting.

## Background

MRSA is a major cause of nosocomial infection in hospitals throughout the world. Rates of infection and colonisation vary substantially between different hospitals both within and between different countries. The UK has one of the highest rates within Europe and the need for improved intervention has been highlighted by experts in infection control [1]. In particular, MRSA is a significant contributor to prolonged hospital stay, poor clinical outcomes and increased healthcare costs amongst surgical patients [2]. The number of death certificates in England and Wales mentioning MRSA has increased from 734 in 2001 to 1,629 in 2005, with an increase of 39% from 2004 to 2005 [3]. Despite there being many reports in the literature of localised successful control of MRSA within the hospital setting, world-wide the incidence of MRSA continues to rise outside of areas such as the Netherlands and Scandinavia, where intensive control has managed to maintain extremely low rates of MRSA [4].

The major method for instituting control is the microbiological identification of patients either colonised or infected with MRSA, followed by isolation of these patients to prevent cross-infection and decolonisation treatment with topical nasal mupirocin and skin disinfection to eliminate carriage [5]. The influence of interventions including active screening and isolation policies on the rates of colonisation and infection caused by MRSA has been comprehensively reviewed recently [1]. This review concluded that, most, intervention studies to date have been poorly designed and poorly controlled, with only one prospective cross-over cohort study, and two prospective cohort studies which were less rigorously controlled. In some studies nurse cohorting in bays was practised on wards and these studies appeared to show a positive effect [6]. The review also included some comprehensive mathematical modelling to try to understand the variables affecting MRSA colonization rates, and concluded that improvements in detection rates and/or isolation capacity should lead to reduced rates of endemic MRSA. However, the review group also found inadequate economic evaluation in all of the studies undertaken, together with a failure to take adequate account of the influence of confounding variables. Their recommendations were that, although current isolation measures appear to have some effect on maintaining lower levels of MRSA colonisation in the UK, further research should be undertaken to provide improved evidence on the clinical effectiveness and cost-effectiveness of MRSA screening and isolation interventions.

*Staphylococcus aureus *strains that express high-level resistance to methicillin (and related agents such as flucloxacillin) produce an additional low affinity penicillin binding protein (PBP2a) (i.e. not inhibited by beta-lactam antibiotics) encoded by the *mec*A gene. Detection of the *mec*A gene in cultures is a reliable surrogate marker for methicillin resistance. Until comparatively recently MRSA detection has largely relied on conventional culture methods on agar plates, which can take 48–72 h to obtain a result [7]. The addition of a broth enrichment step has been shown to improve the sensitivity, but extends the time to result to at least 72 h. However, the length of time to obtain a result limits the usefulness of both these methods, especially with the increasingly short length of hospital stays.

In recent years a number of different molecular methods for the rapid detection of MRSA have been described. The majority of these rely on multiplexed PCR primers to detect genes which identify strains as *S. aureus *(*nuc *is frequently used) and genes which are involved in the expression and mediation of methicillin resistance (*mecA *&*fem*) [8,9]. Such methods are generally only applicable to the identification of purified cultures of staphylococci, and therefore they cannot be used directly on samples [10]. Furthermore, these assays are unable to provide a reliable result from nose and other swabs due to the presence of coagulase negative staphylococci carrying *mecA *giving rise to a false positive result if MSSA are also present. Recently a new rapid test (the IDI-MRSA test) has been developed which is specific for detecting MRSA in nasal swabs. The PCR primers amplify the right hand extremity of the SCC*mec *genetic element, which contains the *mecA*, and *orfX*, an opening reading frame, which is specific for *S. aureus *[11]. An early evaluation on 288 patients has reported a 91.7% sensitivity with a processing time of 1.5 h [12].

A review commissioned by the NHS Health Technology Assessment (HTA) Programme has identified a need for accurate economic assessments of the costs of MRSA control, including the opportunity costs [13]. A recent Dutch study has considered cost and shown that implementation of an aggressive search and destroy MRSA policy within one large University Medical Centre cost €0.28 million per annum. Although an economic analysis suggests that failure to institute this policy would have resulted in greater expenditure, this was not based on prospective study data [14]. An extensive survey of the surveillance data reported in Wales supports the assertion that there are substantial costs associated with MRSA infection, with a deleterious impact on healthcare outcomes on at least half of the patients found to be infected [15]. Much of the attributable cost relates to increased length of stay, along with treatment with a variety of antibiotics, enteral feeding, and intensive care [2].

This paper describes the design, methods and operational aspects of a study investigating the efficacy and cost-effectiveness of rapid MRSA screening and monitoring on surgical wards.

The study has four aims:

1. To measure the impact of screening using rapid MRSA tests versus the most commonly used current test (i.e. culture plate), both in terms of reduction of MRSA cross-infection and improved clinical management and health service resource use.

2. To establish the reliability, turn around time, skills requirement for IDI test in the diagnosis of MRSA versus the most commonly used current test.

3. To assess the cost effectiveness of a screening strategy for MRSA in surgical patients using rapid IDI tests and infection control strategies versus current national MRSA control recommendations, and to model the costs and benefits of different protocols for the early identification and control of MRSA infection in these patients.

4. To produce generalisable protocols and guidelines, in the context of laboratory provision and MRSA levels across the UK, on the use of IDI in the management of MRSA cross infection in surgical patients.

## Methods/Design

### Study Setting and Population

The study is set in a large teaching hospital with over 1,200 beds, providing services to a large population with a wide range of socio-economic, ethnic and age characteristics. All patients admitted to the 7 surgical wards are included in the study. The seven wards include general surgery (2), vascular (1), thoracic (1), ENT (1), trauma and orthopaedics (2) and urology (1). The total capacity of the wards ranges between 20 and 34 beds, and in total is 195 beds; with an average length of stay on the wards of 4.5 days. All of the wards have a limited number of single rooms (2 – 5), none of which have ensuite facilities.

### Inclusion and Exclusion Criteria

All patients aged 18 years plus who have a planned or emergency admission to a surgical ward, including all medical patients and internal transfers are included in the study.

### Overall study design and approach

The study is being carried out as a prospective cluster randomised two-period cross over study. A cross over study design allows a more rigorous means of measuring effectiveness than a simple prospective comparative study between wards. The only difference between the two study periods is the method used for the detection of MRSA in each ward, all other infection control practices are consistent between the wards. The aim of the study is to compare: (i) 'molecular' wards: patients are screened using the rapid IDI-MRSA test; and (ii) 'technical' wards: patients are screened using conventional culture. Results from the IDI_MRSA test are fed back within 2 hours of receipt of the samples to the molecular wards and within 2 days to the technical wards. One study arm contains 4 wards (Wards A), general surgery (1), trauma and orthopaedic (1), ENT (1) and thoracics (1), whilst the other arm contains 3 wards (Wards B), general surgery (1), trauma and orthopaedics (1) and urology (1). In the first period of the cross-over design, wards A were assigned to the molecular group and wards B to the technical group, with the assignment reversed for the second period.

Prior to commencement, educational sessions were held and information leaflets provided to all health care professionals working within the surgical directorate to provide them with information about the study and emphasise the importance of the work. Patient information leaflets, designed to ensure individuals are aware of necessary procedures for themselves, staff and visitors are provided.

Ethical approval was received from East Birmingham Ethics Committee. Written consent from study participants is not required as screening patients for MRSA is hospital policy. An initial two month pilot period was used to allow resolution of all operational and technical problems. This was followed by two 8 month cross-over periods, with one month follow up of study patients at the end of the final period. Wards A were allocated to the molecular arm of the study in the first period and Wards B to the technical arm.

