### Sampling

The study design uses only nasal samples for MRSA screening, for several reasons. Firstly, and most importantly, at the start of the study all published work evaluating the IDI-MRSA assay had used only nasal samples [11]. Secondly a nasal sample is easily obtainable for large scale screening, ensuring comprehensive coverage. Additionally, in previous studies nasal samples have been shown to have a high sensitivity (84%) [16]. Screening swabs are taken from all patients on admission and then if the sample is negative the patient is screened every four days until discharge, and upon the day of discharge. Regular sampling at 4 daily intervals enables the implementation of infection control procedures in a timely manner and the detection of cross infection. Additional samples, for example blood cultures and wound swabs are sent on clinical suspicion as is normal hospital policy.

All samples from the molecular wards are collected by a research nurse at 8 am and 2 pm, Monday to Friday and once daily at 1 pm on a Saturday and Sunday. Samples from the technical wards are transported to the laboratory using the hospital portering service which operates during the day 7 days a week.

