### Rapid communication of results to the wards

All results, both positive and negative, are made available on the laboratory reporting system to which all ward staff have access via a computerised reporting system, immediately upon completion of the test. In addition, all positive MRSA results, both rapid and conventional are telephoned to nurses on the wards, with the time and the person receiving the result documented.

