Swabs from the technical wards are processed throughout the day, Monday to Friday and on Saturday mornings. The swabs are inoculated directly onto chromogenic agar and confirmed as previously described. All MRSA isolates, from both the technical and molecular wards are saved on protect beads and stored at -80C. The first isolate from each patient is epidemiologically typed using staphylococcal interspersed repeat unit (SIRU) typing as previously described and all results entered into Bionumerics™ [20].

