### Data analyses

Analysis will be based on all individuals presenting for admission to the 7 surgical wards (intention to treat), including emergency and planned admissions. Numerical and graphical summaries of all the data will be compiled, including a detailed description of missing data at the ward and individual level.

Sensitivity and specificity will be estimated for PCR and culture tests. Receiver operating characteristic (ROC) curves are not appropriate because this is not a quantitative test. However, the positive predictive value (PPV) and negative predictive value (NPV) will be calculated. We will examine test replicability (i.e. precision) which reflects the variance in a test result that occurs when the test is repeated on the same specimen. Test reliability (e.g. failure rates) and laboratory turn-around time will also be compared.

The main clinical outcome measures will be MRSA cross-transmission rates, antibiotic therapy and MRSA-related morbidity. Secondary outcome measures will include length of in-patient stay, ITU episodes, a final outcome recorded at discharge, and MRSA infection at the outpatient follow-up clinic. Measures of resource use will include the cost of hospital episode and any re-admissions for MRSA.

The numbers of patients becoming infected, the cross-transmission rates and the numbers of MRSA-related deaths within each ward will be compared for the molecular and technical periods. The main analysis will focus on ward by period level data summaries. It seems likely that the number of new MRSA cases observed in each ward in each period will follow a Poisson distribution with mean depending on the size and type of the ward and whether the molecular or technical testing is being used in that period. A non-linear repeated measures random-effects analysis will be used to compare the mean number of cases, rate of cross-infection and number of MRSA related deaths. Ward by period interaction-level covariates could be included in this analysis. Depending on the observed rate of MRSA colonisation or infection and admission to the different wards, a normal approximation to the Poisson distribution may be appropriate, enabling linear modelling techniques to be used.

Further analyses will use linear or non-linear mixed effect models to assess the effects patient-level covariates. Estimates of the difference between the molecular and technical periods adjusted for the effect of covariates will be obtained.

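### The detection test is not the only difference between the arms, so a difference in transmission can be credited to the rapid-screening pathway but not to PCR alone

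*Protocol article*

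**What the plan says.** The Abstract and the section Overall study design and approach both make the claim. The latter reads: "The only difference between the two study periods is the method used for the detection of MRSA in each ward". The same sentence goes on to say that other infection control practices do not differ between wards.

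Other sections of the article describe how each arm works:

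- **Collection (Sampling).** "All samples from the molecular wards are collected by a research nurse at 8 am and 2 pm" on weekdays, with one collection at 1 pm on Saturday and one on Sunday. By contrast, "Samples from the technical wards are transported to the laboratory using the hospital portering service", in the daytime on all seven days.
- **Laboratory days (Laboratory protocols).** Molecular batches are run on weekdays and at weekends. For the other arm, "Swabs from the technical wards are processed throughout the day, Monday to Friday and on Saturday mornings".
- **Parallel culture (Laboratory protocols).** Every molecular swab is plated before its DNA is extracted. PCR-positive swabs also go into enrichment broth, and discrepant plates are incubated for a further 24 h. Technical swabs are plated directly only.
- **Reporting (Rapid communication of results to the wards).** All results go on the laboratory system, and "all positive MRSA results, both rapid and conventional are telephoned to nurses on the wards".
- **Timing.** "Results from the IDI_MRSA test are fed back within 2 hours of receipt of the samples to the molecular wards". For technical wards the stated limit is 2 days. Under Data analyses, "Test reliability (e.g. failure rates) and laboratory turn-around time will also be compared".
- **Costs (Economic analysis).** Each test is costed by observation in the laboratory, counting labour, consumables, capital, maintenance and overheads. The ratio is cost per unit improvement in transmission rate.

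**The concern.** The mechanism under test is earlier identification of carriers. Courier arrangements, laboratory opening days and a second test on the same swab all affect when, or whether, a carrier is identified, and none of them is part of the PCR assay. If they travel with the arm, the trial compares PCR with its own collection, weekend service and added culture against culture as routinely delivered. Aim 1 is worded as a comparison of tests. A reader who accepts the sentence about a single difference would attribute the whole effect to the assay.

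Two further results depend on this. A turnaround counted from laboratory receipt leaves out the wait for the next fixed collection, which the ward does experience. A cost-effectiveness ratio whose numerator covers less than the pathway behind the denominator would be hard to interpret.

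**Working it through.** **1. The statement against the procedures**

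| Feature | Molecular wards | Technical wards |
|---|---|---|
| Collection | Research nurse, fixed times | Porter, daytime |
| Processing days | Seven | Monday to Friday and Saturday morning |
| Tests on each swab | PCR and culture | Culture |

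All three rows differ by arm. The section Implementation of infection control measures standardises and audits what happens after a positive result, but it does not cover these rows.

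**2. Wait before the molecular clock starts**

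The collection times are those under Sampling. The gaps over one week are 6 h (five times), 18 h (four times), 23 h, 24 h and 19 h, which sum to 30 + 72 + 23 + 24 + 19 = 168 h. If swabs are taken evenly over 24 h, the mean wait is the sum of squared gaps divided by 2 × 168:

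(5 × 36 + 4 × 324 + 529 + 576 + 361) / 336 = 2942 / 336 = 8.8 h, maximum 24 h.

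Adding the 2 h limit gives up to about 10.8 h on average from swab to result. If swabs are taken only between 08:00 and 20:00, the mean wait is 10.1 h.

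**3. The same quantity in the technical arm**

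The article gives no laboratory hours. Assume opening at 08:00, weekday closing at 17:00 or 20:00, Saturday closing at noon, and no portering time. The longest closure, Saturday noon to Monday 08:00, is 44 h, or 44/168 = 26% of the week (24% of swabs if taken only from 08:00 to 20:00).

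- Closing at 17:00, swabs over 24 h: (5 × 15² + 44²) / 336 = 3061 / 336 = 9.1 h.
- Closing at 20:00, swabs over 24 h: (5 × 12² + 44²) / 336 = 2656 / 336 = 7.9 h.
- Swabs from 08:00 to 20:00 only: 8.8 h and 6.4 h respectively.

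So the technical mean is about 6 to 9 h, and the maximum 44 h.

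**4. How much comes from missing weekend processing**

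With seven-day processing at the same hours, the four technical means become 4.7, 3.0, 3.4 and 0.0 h. The differences are 9.1 − 4.7 = 4.4, 7.9 − 3.0 = 4.9, 8.8 − 3.4 = 5.4 and 6.4 − 0.0 = 6.4 h, or about 4 to 6 h. The stated feedback limits differ by up to 48 − 2 = 46 h. This sets a mean against a difference of limits, so it indicates relative size only.

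**5. How much the parallel culture could add**

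The plate can add only carriers whom PCR misses. The Background cites a sensitivity of 91.7%, and Sample size assumes 5% colonised among 5000 patients: 5000 × 0.05 = 250 carriers on admission, and 250 × (1 − 0.917) = about 21. That is a ceiling for admission carriers at those two figures, since culture may miss some of the same patients.

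**The case against.** The best defence is that the sentence, read to its end, concerns infection control practice. That practice is standardised and audited on all wards, while collection and laboratory workflow are openly described and can be seen as part of a detection pathway. Aim 3 and the Economic analysis speak of a screening strategy, and the study is meant to fit routine NHS practice, so portering and limited weekend culture may be intended features of the comparator. This explains why the arms were run as they were. It does not make the sentence true, because laboratory days and couriers are not a detection method.

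Several stronger readings may tempt a reader, and the documents do not support them:

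- **That no effect can be credited to PCR.** The assay probably accounts for most of the speed difference (step 4 of the working).
- **That nurse collection or nurse presence explains a benefit.** Mean waits before processing are no clearly shorter in the molecular arm, and research nurses audit and collect data for all study patients. Only the swab pick-up differs.
- **That broth enrichment explains a benefit.** It is used only on swabs already positive by PCR.
- **That the plan costs PCR alone.** The Economic analysis sets out to estimate differences in resources used between the two kinds of ward.
- **That culture-only carriers on molecular wards are certainly acted on.** This follows from a plain reading of the reporting section, but the wording could also mean rapid results for one arm and conventional results for the other.
- **That turnaround is concealed.** The article says openly that the 2 h runs from receipt, and Data collection records the time each sample is taken.

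**Conclusion.** The point stands as a contradiction within the article that limits what may be concluded. Collection, laboratory days and parallel culture all differ by arm, so the trial estimates the effect of the rapid-screening pathway as delivered against the culture pathway as delivered. Nothing in the article separates PCR from the rest.

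The size is moderate. Missing weekend processing accounts for roughly 4 to 6 h of mean delay in the technical arm, small beside the stated feedback limits. That estimate rests on assumed laboratory hours, evenly spread swabs and no portering time. The molecular wait of 8.8 h rests on the stated schedule and on swabs spread over 24 h. It is similar to the technical wait, so the time before processing favours neither arm on average, although the technical maximum is longer (about 44 h against 24 h).

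**What to change.** 1. Reword the Abstract and Overall study design and approach to list the three differences, and limit conclusions to the rapid-screening pathway against the culture pathway.
2. Besides laboratory turnaround, report time from swab taken to result reported in both arms, split by weekday and weekend. Time taken is already recorded, and so is the time of telephoning for positive results.
3. State whether culture results from molecular wards reach the ward. If they do, tabulate carriers first notified by PCR and those first notified by culture only.
4. In the cost-effectiveness ratio, match costs to the pathway that produced the effect. Include collection, transport and weekend laboratory work, which are not named among the test costs, and show results with and without the parallel culture.

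The Discussion says recruitment is nearly complete. These are changes of wording and analysis, and the conduct of the study need not change. The price is a narrower claim and possibly a higher stated cost for the molecular arm.
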